#### Anthropometric data

Body mass (Kg), height (meters) and subsequently the BMI will be obtained through the ratio between body mass and height squared (kg/m^2^) [22]. The ideal body mass (Kg) will be obtained through the estimate given by *Diretrizes Brasileiras de Ventilação Mecânica da AMIB* [15]. The height will be measured by means of an inextensible and inelastic anthropometric tape of 1.5 m and an interval of 0.01 m. The semi-wingspan will be obtained by measuring the distance between the sternum and the tip of the middle finger of one hand (hemi wingspan) [23, 24]. In an effort to minimize the leak and the factors that can predispose to a mask leak, the beard/facial hair will be removed before the institution of the NIV.

#### Vital signs and respiratory effort

SpO_2_ will be measured using pulse oximetry (DX2010, Dixtal, Manaus, AM, Brazil), and BP and heart rate (HR) will be assessed through digital monitoring (DX2010, Dixtal, Manaus, AM, Brazil). Hypotension will be considered when SBP < 80 mmHg or mean arterial pressure < 60 mmHg) within 24 h after NIV. RR will be obtained by a plethysmographic signal provided by the VM monitor (SERVO-S, Maquet Critical Care, São Paulo, SP, Brazil). The respiratory effort will be qualified by inspection when the patient develops tachypnea, use of accessory muscles, flapping of the nose, change in breathing pattern, shallow breathing, and abnormal movements of rib cage [25]. Such measures will be performed before and after 1 h of NIV institution.

#### Ventilatory parameters

The following ventilatory variables will be monitored in the mechanical ventilation: Vt, MV, Ppeak, RR, FiO_2_, Ti, Te, air leak, VMi, and VMe. Such variables will be obtained before and after the application of NIV. Such measures should be carried out after 1 h of NIV adaptation.

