**Fig. 1 Fig1:**
[figure not shown]
Flowchart of the study

NIV will be instituted in CPAP or bi-level positive airway pressure (BiPAP) mode with expiratory positive airway pressure (EPAP) and inspiratory positive airway pressure (IPAP) levels of up to 10–12 cmH_2_O. NIV will be used for 30 min to 1 h for patients with COVID-19, with gas analysis before and after this period. Sessions in non-COVID-19 patients can last up to 2 h, and NIV can be used intermittently, as long as there is no clinical worsening or signs of failure [13, 14].
CPAP: hypoxemic respiratory failure, with positive expiratory end pressure (PEEP) between 5 and 12 cmH_2_O and FiO_2_ minimum to maintain SpO_2_ ≥ 94%BIPAP: hypercapnic respiratory failure, start with IPAP necessary to maintain SpO_2_ > 94% and with maximum levels up to 10–12 cmH_2_O. Tidal volume up to a maximum of 9 ml/Kg/predicted weight, EPAP (PEEP) between 6 and 8 cmH_2_O and FiO_2_ minimum enough for SpO_2_ ≥ 94%

NIV will be performed by a conventional mechanical ventilator, preferably by SERVO-S (Maquet Critical Care, São Paulo, Brazil), or by the one available at each research center. The criteria for its interruption will be those of clinical worsening (determined by the medical team) such as the occurrence of hemodynamic instability, depression of the cognitive state, psychomotor agitation, lack of airway defense, lack of adaptation to the interface, and severe bronchospasm [15]. Success or reduction in the severity of RF will be considered by the oxygenation index through the PaO_2_/FiO_2_ > 200, reduction in RR < 30 bpm and SpO_2_ ≥ 94% [12, 16].
NIV Owner group (experimental group)
Patients with suspected or confirmed COVID-19 undergoing NIV with an Owner maskPatients with RF due to causes unrelated to COVID-19 submitted to NIV with Owner maskNIV orofacial group (control group)
Patients with suspected or confirmed COVID-19 undergoing NIV with conventional orofacial maskPatients with RF due to causes unrelated to COVID-19 submitted to NIV with conventional orofacial mask

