#### Relevant concomitant care permitted or prohibited during the trial {11d}

All concomitant care and interventions are permitted other than concomitant receipt of any other experimental treatment. Patients will use the drug therapy indicated by the attending physician. The NIV will be implemented by using a diving mask adapted into a mechanical ventilator, a HEPA filter in the expiratory branch, and a heat and moisture exchanger (HME) filter in the trachea Y, with it being performed twice a day for 60 min., with positive pressure levels of up to 10–12 cmH_2_O whenever there is a clinical indication to do so [12].

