#### Secondary outcome measure

In-hospital mortality [period: up to 30 days]Differences in the PaO_2_/FiO_2_ ratio regarding the baseline values (before NIV) [period: 48 h]Improvement in the PaO_2_/FiO_2_ ratio after beginning NIV [period: 1 h after NIV]PaCO_2_ levels [period: 1 to 12 h after NIV]Blood pressure (BP) and hypotension incidence (SBP < 80 mmHg or mean arterial pressure < 60 mmHg) [period: up to 2 h after NIV]Time between beginning NIV and its endICU time [time period: up to 30 days]Length of hospital stay of patients who used NIVAdverse events of the mask [period: obtained at pre-hospital discharge]Comfort of the patient with the mask (visual analog scale—VAS) [period: obtained at pre-hospital discharge]Satisfaction level (PGIC) after using NIV [period: obtained at pre-hospital discharge]NIV success rate with masks [deadline: 1 h since the beginning of NIV]Tidal volume (Vt), minute volume (MV), peak pressure (Ppeak), respiratory rate (RR), FiO_2_, inspiratory time (Ti), expiratory time (Te), air leak, inspiratory minute volume (VMi), and expiratory minute volume (VMe) obtained in NIV [period: 1 h after NIV]

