#### Sample size {14}

The calculated sample size is based on an OIT rate of 30.2% for patients with COVID-19 who require mechanical ventilation [17]. Thus, we estimate that a total of 126 patients (63 in each group) would provide 80% of power to detect an absolute reduction of 20% of the primary result [18], with the adoption of a two-tailed model and a significance level of 0.05. Assuming a loss of follow-up of 20%, 151 patients will be recruited.

Assuming an intubation rate of 61% for patients with acute respiratory syndrome requiring mechanical ventilation [19], we calculated that a total of 194 (97 in each group) patients would provide 80% power to detect an absolute reduction 20% of the primary result [18], with the adoption of a two-tailed model and a significance level of 0.05. Assuming a loss of follow-up of 20%, 232 patients will be recruited. The sample size calculations were performed using the G*Power software (Version 3.1.9.6) [20]. A total of 383 patients will participate in the study, 151 in the group of patients with suspicion or confirmation SARS-CoV-2, and 232 for those with respiratory syndrome who require non-invasive ventilation.

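### Air leak and the other on-ventilator secondary outcomes are timed at 1 h of NIV, although a compliant COVID-19 session may end from 30 min onwards

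*Protocol article*

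**What the plan says.** All places are in the protocol article.

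- **Reading time, methods.** The section Ventilatory parameters lists tidal volume, minute volume, peak pressure, respiratory rate, FiO2, inspiratory and expiratory time, air leak, and inspiratory and expiratory minute volume. It first says "Such variables will be obtained before and after the application of NIV", then fixes the time: "Such measures should be carried out after 1 h of NIV adaptation".
- **Reading time, outcome list.** Secondary outcome measure gives the same variables, ending "expiratory minute volume (VMe) obtained in NIV [period: 1 h after NIV".
- **Session length, COVID-19.** The text under Intervention description {11a} says "NIV will be used for 30 min to 1 h for patients with COVID-19, with gas analysis before and after this period".
- **Session length, other patients.** The same section says "Sessions in non-COVID-19 patients can last up to 2 h, and NIV can be used intermittently". It sets a ceiling and no minimum.
- **A different session length.** Relevant concomitant care {11d} describes NIV through the diving mask, "with it being performed twice a day for 60 min".
- **Stopping.** Intervention description {11a} includes poor adaptation to the interface among the reasons to interrupt NIV. Criteria for discontinuing {11b} lists reasons to interrupt the experimental treatment, among them a ventilator-detected leak above 24 l/min and discomfort with the mask.
- **Population.** Sample size {14} plans 383 patients, "151 in the group of patients with suspicion or confirmation SARS-CoV-2".

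**The concern.** Apart from respiratory rate and FiO2, which can in principle be observed without the mask, these variables exist only while the patient is being ventilated through it. For a COVID-19 patient under {11a}, 1 h is the longest permitted session. At best the reading falls at the moment the session ends. A patient who follows the protocol with a 40-min session has no value at the stated time.

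Leak is not a marginal variable here. Explanation for the choice of comparators {6b} justifies the Owner mask by reduced leakage in a pilot study, and the background builds the aerosol-safety argument on the seal. Ventilator-measured leak is the trial's direct test of that property, and the timing gap falls on the COVID-19 patients, in whom aerosol matters most. A reading that was never taken cannot be recovered by a later analysis rule.

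**Working it through.** **1. What does not depend on this point.** With p1 and p2 the two intubation rates and p̄ their mean, the usual formula for two proportions (pooled variance under the null, two-sided 0.05, 80% power, no continuity correction) is

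n per arm = [1.96·√(2p̄(1−p̄)) + 0.8416·√(p1(1−p1) + p2(1−p2))]² / (p1−p2)²

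- COVID-19, 0.302 against 0.102: (1.1129 + 0.4628)²/0.04 = 62.1, so 63 per arm, as stated.
- Non-COVID, 0.61 against 0.41: (1.3856 + 0.5830)²/0.04 = 96.9, so 97 per arm, as stated.

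Both concern intubation and use no ventilator reading.

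**2. Reading time against session length.**

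| Population and source | Session length | On-mask value at 1 h? |
|---|---|---|
| COVID-19, {11a} | 30 min to 1 h | Only if the session runs the full hour |
| Diving mask, {11d} | 60 min, twice a day | Yes, at the end of a completed session |
| Non-COVID, {11a} | Up to 2 h, no minimum | Only if the session lasts 1 h or more |

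The {11d} sentence does not withdraw the 30-min allowance in {11a}. If it governed the Owner arm alone, the chance of reaching the reading would differ by arm.

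**3. Could the 1 h be counted from another point?** If the outcome list meant 1 h after NIV had ended, nobody would have an on-ventilator value. The Fig. 2 legend (t1 start, t2 1 h after) and the wording of Ventilatory parameters both point to counting from the start.

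**4. How many patients.** The COVID-19 population is 151/383 = 39.4% of recruits. The document gives no distribution of session length, so the number without a 1-h value could be anything from 0 to 151. For an assumed range:

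- 25% of COVID-19 sessions end early: 0.25 × 151 ≈ 38 without a value, 151 − 38 = 113 with one, about 57 per arm.
- 50% end early: 0.50 × 151 ≈ 76 without a value, 75 with one, about 38 per arm.

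These counts are before any other loss.

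**5. Could the missing values be selective?** No section says who chooses 30 min or 1 h, or on what grounds. If the choice is unrelated to mask and patient state, short sessions cost precision only. The stopping reasons are different, because one of them is the measured variable itself. An illustration for that route alone, with assumed values: leak is normal with SD 8 l/min, and a reading exists only at or below 24 l/min in both arms. With a = (24 − μ)/8, the mean among readable patients is μ − 8·φ(a)/Φ(a).

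- μ = 16: a = 1, 16 − 8 × 0.2420/0.8413 = 13.7; 84% readable.
- μ = 24: a = 0, 24 − 8 × 0.3989/0.5 = 17.6; 50% readable.

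A true difference of 8 l/min would appear as 17.6 − 13.7 = 3.9. This shows the direction of a possible distortion. It says nothing about short sessions ended for other reasons.

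**The case against.** The other side has several good arguments.

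- **The 60-min statement in {11d}.** If sessions run 60 min, a completed session reaches the reading. This stands as far as it goes, but the sentence names only the diving mask and conflicts with {11a}. What is documented is an inconsistency that leaves the reading time unsafe, and not a settled rule of short sessions.
- **The outcome list may describe a window.** The section PaO2/FiO2 ratio restates its own 1-h and 48-h periods as within 1 h and within 48 h. Read that way, a 40-min end-of-session value would count. This stands for the outcome list. Ventilatory parameters is stricter and sets the reading after 1 h.
- **Selection.** A reader might infer that patients with a 1-h value are a selected group that differs by mask, because an unblinded team decides session length in response to leak and tolerance. The document does not say that. The link between leak or intolerance and stopping appears only in the interruption rules of {11a} and {11b}. Selection is possible by that route and is not shown for compliant short sessions.
- **Missing-value rules belong in the analysis plan.** True, and their absence is not the point. The point is a measurement time that the protocol itself fixes.
- **Limited reach.** These are secondary outcomes, and the pre-discharge questionnaire also asks about leaks whatever the session length. That stands, although the questionnaire is subjective and does not replace the ventilator reading.

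**Conclusion.** The point holds in a limited form. The 1-h reading time in Ventilatory parameters, and less strictly in the outcome list, does not fit the 30-min to 1-h COVID-19 session in {11a}, and {11d} gives a third statement that does not settle the matter. Under {11a}, a compliant session shorter than 1 h yields no on-mask value at the stated time.

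The size is unknown. The 39.4% is the share of recruits in the COVID-19 population and should not be read as the share affected; the 38 to 76 patients rest on an assumed 25% to 50% of early-ending sessions. A reader might also conclude that these outcomes cannot be scored at all in COVID-19 patients. The documents do not support that, since sessions lasting the full hour can be read. Nor do they establish bias between the masks. The primary outcome and both sample sizes are unaffected. This is an inexpensive improvement to secondary outcomes, worth making because leak is the property for which the Owner mask was chosen.

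**What to change.** Reconcile Intervention description {11a}, Relevant concomitant care {11d}, Secondary outcome measure and Ventilatory parameters on session length and reading time. Which session length applies is for the investigators; the measurement change below works with any of them.

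1. In both arms and both populations, define each on-ventilator outcome as the on-mask reading at one common early time, for example 30 min of the first session.
2. If the session ends earlier for any reason, use the last on-mask reading. This is needed for early stops and also for short non-COVID sessions, which have no stated minimum.
3. Record the clock time of every reading and the reason if the session ended before the common time.
4. Compare the arms as randomised, including every randomised patient with any on-mask value.
5. Keep the 1-h reading as an additional description for sessions that last that long.

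The cost is one timed reading from the ventilator display and revised wording in the sections on outcomes and ventilatory parameters. On the downside, reading times become somewhat mixed, the outcome describes early NIV, and patients already enrolled can contribute only the readings already taken.

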#### Arterial blood gas analysis

Arterial blood gasses will be obtained according to the routines of each center participating in the research. For research purposes, the gasometric variables will be assessed at the baseline (before NIV) and from 1 to 12 h from the beginning of NIV.

#### PaO_2_/FiO_2_ ratio

The difference in PaO_2_/FiO_2_ ratio regarding the baseline values (before NIV) will be assessed within 48 h, and the improvement of such relationship after the beginning of NIV, within 1 h after NIV.

#### Comfort of the NIV face mask

The comfort provided by facial masks will be assessed before hospital discharge using the VAS, if the patient presents a satisfactory response to NIV with the Owner mask and the conventional orofacial mask and presents a stable clinical condition.

#### Adverse effects of the NIV face mask

The adverse effects of wearing the masks will be assessed before the patient’s discharge from the hospital using a questionnaire consisting of 11 questions regarding: pain in the face region (forehead, nose, cheeks or chin), leaks (around the eyes and around the mouth), dryness (mouth, throat and nose), pressure, irritation, or claustrophobia [26].

#### Global Perception of Change

The Patients’ Global Impression of Change (PGIC) questionnaire will be used to assess the perception of improvement in individuals submitted to NIV use with the Owner mask before the patient’s discharge from hospital [27].

#### Plans to promote participant retention and complete follow-up {18b}

The procedures will be interrupted due to the occurrence of unexpected events, in which the necessary assistance will be provided immediately. It is noteworthy that the data collection will not interfere in the hospital routine of the evaluated patients nor in any medical treatment that the patient is developing. If necessary, the right to immediate, full and free healthcare will be guaranteed.

The patients will not incur any expenses with transportation, food, exams, and materials to be used or expenses of any other nature to participate in this study. Compensation will occur in the event of any damages resulting from the study. Patients will also receive clarification on any questions about the procedures, risks, benefits, and other issues related to the research. The patient may stop participating in the study without prejudice to continuing their treatment. Medical treatment and compensation will be offered if there is damage to the patient’s health caused by this study.

#### Data management {19}

The data will initially be inserted in an Excel spreadsheet with double data entry and will be checked weekly by the researchers responsible for each hospital before being sent to a spreadsheet where all of this data will be computed and will be under the responsibility of the project coordinator. All variables will be categorized and coded for security, where only those responsible for the co-participating institutions will have access to filling, checking, and storing. Researchers will be responsible for evaluating and collecting results from the baseline to the end of the study. All data will be verified again by the research coordinator and the associates responsible for each hospital unit involved, as well as by the DSMB.

#### Confidentiality {27}

The data of the evaluated patients will be collected and identified by a single identification of the study subject, preserving anonymity, as well as the samples collected through the study. The record linking the study subject’s identification with the patient’s identification information will be kept confidential at each recruitment location.

#### Plans for collection, laboratory evaluation, and storage of biological specimens for genetic or molecular analysis in this trial/future use {33}

These plans are not yet in place.

### Statistical methods

#### Statistical methods for primary and secondary outcomes {20a}

The SPSS software program (version 25.0, IBM, Armonk, NY, USA) will be used for data analysis using the Generalized Estimation Equations (GEE) model. The normality of the data will be assessed using the Kolmogorov-Smirnov test. Identity function, unstructured work correlation matrix, and covariance matrix of the robust estimator will be used using the Bonferroni post hoc test when significant. The chi-squared test will be used to compare the proportions of categorical variables studied in the groups and the Mann-Whitney *U* test to compare the distributions of continuous variables between groups (*p* < 0.05). Analysis by intention-to-treat will be performed to include patients who did not allow analysis of outcomes.

The effect size will be estimated according to Cohen [28], who suggested a cutoff value greater than or equal to 0.8 representing a large effect size, between 0.8 and 0.2 as a medium effect size, and values below 0.2 as a small effect size. The same will be calculated using the variation obtained before and after the intervention, as well as for the post-intervention moment between the groups analyzed. The effect size will be calculated using [name] Effect Size Calculator [http://www.uccs.edu/lbecker/].

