### Data collection and management

#### Plans for assessment and collection of outcomes {18a}

The data of each research subject (including discontinued subjects) will be registered in the database quickly, completely, and accurately through an electronic form made available to each researcher in their respective hospital and mandatory to be completed and checked by the researchers investigated by the study in each hospital institution. The data administrator will review and modify the data according to the check of the researchers where the research is being carried out.

Analysis of clinical, sociodemographic data, age, sex, and body mass index (BMI) will be performed. An analog pain assessment will subsequently be performed using the VAS [21] and the perception of effort using the Modified Borg Scale. Clinical severity will be quantified using the Simplified Acute Physiological Score III (SAPS III) based on data obtained from the patient’s medical record. The presence of comorbidities, smoking, symptoms, confirmation of SARS-CoV-2 infection, origin of the patient, history of exposure, and complications that may occur during hospitalization will be recorded. The OTI rate will be obtained in patients who have undergone NIV, as well as in-hospital mortality within a period of up to 30 days.

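### The primary intubation comparison is an unadjusted chi-squared test although SAPS III and pre-NIV PaO2/FiO2 are collected: a missed efficiency, not a power error

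*Protocol article*

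**What the plan says.** The protocol article, Statistical methods {20a}, fixes the test for binary outcomes: "The chi-squared test will be used to compare the proportions of categorical variables studied in the groups". It names the Mann-Whitney U test for continuous variables between groups. The same section also names a GEE model (identity function, unstructured working correlation, robust variance), without saying which outcomes it serves and without listing covariates. Methods for additional analyses {20b} repeats all three methods.

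OTI is one yes/no result per patient, so the chi-squared test is the named method that fits it.

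Two candidate covariates are collected. Plans for assessment and collection of outcomes {18a} states: "Clinical severity will be quantified using the Simplified Acute Physiological Score III (SAPS III"), from the medical record. The section on gas exchange states that the difference in the PaO2/FiO2 "ratio regarding the baseline values (before NIV) will be assessed within 48 h", so a pre-NIV value is needed in any case. Neither covariate is given a role in the analysis.

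Sample size {14} powers two populations separately. Each has a 20-point absolute reduction and 80% power, "with the adoption of a two-tailed model and a significance level of 0.05".

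**The concern.** A severity score and baseline oxygenation would ordinarily be expected to predict both intubation and later gas exchange. Where a baseline variable predicts the outcome, a model that includes it generally tests the arm effect with more power than an unadjusted test on the same patients. Both populations are of modest size and planned at about 80% power. Since the measurements are already being made, leaving them out of the primary comparison saves almost nothing. What is at stake is some power for OTI and some precision for the blood-gas outcomes.

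**Working it through.** **Inputs from Sample size {14}.**
- COVID: "OIT rate of 30.2% for patients with COVID-19 who require mechanical ventilation", so 30.2% against 10.2%, with "a total of 126 patients (63 in each group").
- Non-COVID: "Assuming an intubation rate of 61% for patients with acute respiratory syndrome requiring mechanical ventilation", so 61% against 41%, with 97 per arm.
- Two-sided alpha 0.05 (z = 1.960), power 80% (z = 0.842), equal allocation.

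**Step 1: reproduce the plan's figures.** Pooled formula without continuity correction, with p̄ the mean of the two rates:

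n per arm = [1.960·√(2p̄(1−p̄)) + 0.842·√(p1(1−p1) + p2(1−p2))]² / (p1−p2)²

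- COVID: p̄ = 0.202; (1.960·0.568 + 0.842·0.550)² / 0.04 gives 63. Power at 63 is 80.6% (exact chi-squared power 81.4%).
- Non-COVID: p̄ = 0.51; (1.960·0.707 + 0.842·0.693)² / 0.04 gives 97. Power at 97 is 80.0% (exact 80.7%).

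Both stated sizes reproduce.

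**Step 2: power with adjustment.** The document gives no prognostic strength, so it is assumed and varied. Each setting has 4000 simulated trials with one standard normal baseline score and the marginal rates held at the document's values. The log odds ratio per SD is 0, 0.5, 1.0 or 1.5. The chi-squared test is compared with the likelihood-ratio test for arm in a logistic model that includes the score.

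| Population | AUC of score | Chi-squared | Adjusted | Difference (points) |
|---|---|---|---|---|
| COVID, 63 per arm | 0.50 | 81.8% | 82.9% | 1.1 |
| | 0.64 | 81.1% | 83.4% | 2.3 |
| | 0.74 | 81.6% | 87.1% | 5.5 |
| | 0.82 | 81.4% | 90.9% | 9.5 |
| Non-COVID, 97 per arm | 0.50 | 81.1% | 80.9% | −0.2 |
| | 0.63 | 80.3% | 82.1% | 1.8 |
| | 0.74 | 81.5% | 87.5% | 6.0 |
| | 0.81 | 80.3% | 91.1% | 10.8 |

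A score with AUC 0.50 carries no information. The 1.1 points in the first row therefore reflect the type of test and simulation error, and the other COVID gains may be about a point generous.

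As a rough cross-check, n·(1−R²) gives the number per arm needed for 80% power. At R² of 0.05, 0.10 and 0.20 this is 60, 57 and 51 (COVID) and 93, 88 and 78 (non-COVID).

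**Step 3: room for covariates.** Expected intubations are 63·0.302 + 63·0.102 = 19.0 + 6.4, about 25, in the COVID population. In the non-COVID population they are 97·0.61 + 97·0.41 = 59.2 + 39.8, about 99.

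**Step 4: continuous outcomes.** The 48 h PaO2/FiO2 outcome is defined as a difference from baseline, so the fair comparator is a change score. With equal variances and baseline-to-follow-up correlation ρ, relative to the variance of a single follow-up value:
- change score: 2(1−ρ)
- ANCOVA: 1−ρ²
- ratio of ANCOVA to change score: (1−ρ²) / [2(1−ρ)] = (1+ρ)/2

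This gives 0.65, 0.75 and 0.85 at assumed ρ of 0.3, 0.5 and 0.7. The gain shrinks as ρ rises. These ratios concern comparisons of means, not the Mann-Whitney test itself.

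**The case against.** Several stronger readings are tempting, and the document does not support them.

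- *The trial is underpowered because of this test.* It is not. The sample size was set for the unadjusted comparison and reproduces. Recruitment of 151 and 232 is planned; if losses were small, about 75 and 116 per arm would give the chi-squared test about 87% power in each population.
- *A definite amount of power is lost.* No prognostic strength is given. Eligibility limits on SpO2 or PaO2/FiO2 may narrow the baseline range and weaken prediction, and the gain can be close to nil.
- *All continuous outcomes are compared without their baseline.* A GEE model is named alongside the Mann-Whitney test, and the legend of Fig. 2 lists times from start to 48 h, so the baseline may already enter as a time point. What can be said is that the article does not assign methods to outcomes and lists no covariates.
- *ANCOVA would roughly halve the variance at ρ = 0.7.* That figure (0.51) is relative to follow-up values alone. Against the difference from baseline that the plan defines, the ratio is 0.85.
- *Chance imbalance in severity invalidates the test.* Under randomisation the error rate of the unadjusted test already allows for it.
- *Both covariates are available at baseline for everyone.* Blood gases follow each centre's routine, eligibility is possible on SpO2 alone, and the timing of the SAPS III data is not given.

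The best remaining objection is that covariate lists usually belong in the SAP, which is not shown. That would answer silence. Here the article names a specific unadjusted test that fits the primary outcome, which is a choice that can be improved.

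**Conclusion.** The point stands as a missed efficiency in a stated choice of test. The chi-squared test is valid and delivers the planned power of about 80%; no figure needs correcting. Adjusting OTI for baseline severity would add about 0 to 2 points of power if the covariates are weak, about 6 at AUC 0.74, and 9 to 11 at AUC 0.81 to 0.82. These sizes rest on assumed prognostic strength, on the planning rates, and on one score tested by likelihood ratio within each population. They do not measure the exact two-covariate model and risk-difference summary proposed below. For blood gases, the benefit over a change score is a variance ratio of (1+ρ)/2 with ρ assumed. This is a worthwhile improvement at little cost, not a defect that threatens the trial's conclusions.

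**What to change.** 1. **OTI.** Within each of the two separately powered populations, make the primary comparison a logistic model with arm, SAPS III and baseline PaO2/FiO2, reported as a standardised risk difference with 95% CI. Keep the chi-squared test as a sensitivity analysis. Use SAPS III only if it is scored from data before randomisation, and state that timing.
2. **Pooling.** A single model across both populations would answer a different question from the two powered comparisons. If a pooled analysis is also wanted, include COVID status: the assumed control rates of 30.2% and 61% imply an odds ratio of (0.61/0.39)/(0.302/0.698), about 3.6.
3. **PaO2/FiO2 and PaCO2.** Use the planned GEE, or ANCOVA, with the patient's own pre-NIV value as covariate in place of an unadjusted Mann-Whitney test, and say which outcomes the GEE serves.
4. **Safeguards.** Hold the OTI model to these two covariates, given about 25 expected events in the COVID population. Set in advance a rule for missing baseline gases that keeps every randomised patient in the analysis.

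The cost is analysis wording plus the missing-baseline rule; no extra patients or planned measurements are needed. The wording should be fixed before anyone choosing the model sees outcomes by arm.

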### Outcomes {12}

#### Primary outcome measure

OTI rate in patients with or without suspicion or confirmation of SARS-CoV-2 infection submitted to NIV with Owner mask or conventional orofacial mask.

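### Stay in ICU and hospital is compared without separating deaths, and the intubation rate counts death without intubation as a non-event; both mislead if deaths differ between arms

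*Protocol article*

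**What the plan says.** All references are to the protocol article.

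- **Primary outcome measure:** the article defines it as "OTI rate in patients with or without suspicion or confirmation of SARS-CoV-2 infection submitted to NIV with Owner mask or conventional orofacial mask". Death is not a component, and no window is given there. Item 18a takes the rate over patients who underwent NIV and, in the same sentence, mentions in-hospital mortality up to 30 days.
- **Secondary outcome measure:** the list includes in-hospital mortality and ICU time (both to 30 days), hospital stay over all NIV users, and NIV duration from start to finish. None of the times is limited to survivors or split by how it ended.
- **Statistical methods (item 20a):** after a general reference to GEE, proportions go to a chi-squared test and the Mann-Whitney U is the "test to compare the distributions of continuous variables between groups". The additional-analyses section (20b) repeats both tests.
- **Non-adherence and missing data (item 20c):** only intention-to-treat and per-protocol analyses are named. No section ranks deaths worst, censors at death or treats death as a competing event.

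**The concern.** Stay is cut short by death. Someone who dies on day 2 has a two-day stay and, in a rank test on all patients, sits beside the fastest recoveries. The Discussion lists shorter stay, with avoided intubation and lower mortality, among the crucial outcomes in this field, so a shorter stay will be read as benefit.

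The primary has the same weakness. A patient who dies without intubation stays in the denominator as a non-event, so an arm with more such deaths has a lower OTI rate. The Background and Discussion themselves warn that delayed intubation is prognostically unfavourable, and the treating teams are not blinded to the mask. A shift from intubation to death without intubation is therefore a pattern this trial should be able to see.

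**Working it through.** **1. The plan's own sample size.** Inputs from Sample size (item 14): "OIT rate of 30.2% for patients with COVID-19 who require mechanical ventilation"; "Assuming an intubation rate of 61% for patients with acute respiratory syndrome requiring mechanical ventilation"; each group size "would provide 80% of power to detect an absolute reduction of 20% of the primary result" with a "two-tailed model and a significance level of 0.05".

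n per arm = [1.960·√(2p̄(1−p̄)) + 0.842·√(p1(1−p1)+p2(1−p2))]² / (p1−p2)²

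- COVID, 30.2% vs 10.2%, p̄ = 0.202: (1.960·0.5678 + 0.842·0.5499)² / 0.04 = 62.1, so 63.
- Non-COVID, 61% vs 41%, p̄ = 0.51: (1.960·0.7070 + 0.842·0.6927)² / 0.04 = 96.9, so 97.

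Both planned figures reproduce, with power 80.6% and 80.0%. They rest on OTI alone, with no allowance for death without intubation.

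**2. Primary outcome.** Keep the planned OTI rates and add assumed proportions dying without intubation (control vs Owner). Power is for a two-sided 0.05 test at the planned n.

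| Dead without OTI | OTI-or-death, COVID | Power | OTI-or-death, non-COVID | Power |
|---|---|---|---|---|
| 5% vs 5% | 35.2% vs 15.2% | 74.0% | 66% vs 46% | 80.6% |
| 5% vs 15% | 35.2% vs 25.2% | 22.9% | 66% vs 56% | 29.6% |
| 5% vs 25% | 35.2% vs 35.2% | no difference | 66% vs 66% | no difference |

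In every row the OTI-only test keeps 80.6% and 80.0% power to declare benefit. The last row is an extreme, chosen to show that the primary cannot tell the cases apart.

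**3. Stay.** Assumptions, none from the documents: both arms share the same stay if alive (lognormal, median 14 days, log-SD 0.5); deaths occur at median 6 days (log-SD 0.6); stays are capped at 30 days. Each setting had 10,000 simulated trials and a two-sided Mann-Whitney test at 0.05. The table gives the share of trials significantly favouring the higher-mortality arm (nominal 2.5%; in the 20% vs 20% row, one fixed arm).

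| Mortality | n per arm | Raw stay | Free days to day 30, death = 0 |
|---|---|---|---|
| 20% vs 20% | 63 | 2.5% | 2.5% |
| 20% vs 20% | 97 | 2.4% | 2.3% |
| 30% vs 20% | 63 | 10.3% | 0.2% |
| 30% vs 20% | 97 | 13.9% | 0.1% |
| 40% vs 20% | 63 | 28.3% | 0.0% |
| 40% vs 20% | 97 | 41.6% | 0.0% |

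Smaller repeat runs gave 10% and 13% to 14% at 30% vs 20%, and 29% to 31% and 40% to 43% at 40% vs 20%.

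A second set of assumptions (stay if alive: median 12 days, log-SD 0.6; deaths spread evenly over days 1 to 8) gave 12.4% and 17.8% at 30% vs 20%, and 36.4% and 52.0% at 40% vs 20%. With deaths ranked worst these fell to 0.2% or less.

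**The case against.** **Silence, not error.** The article never says that deaths are scored as short stays or as successes, does not map tests to outcomes, and condenses a fuller document. A reader might infer that the plan deliberately treats death as favourable; the text does not support that. What stands is a consequence of what it does fix: stay over all NIV users, a rank test for continuous variables, and OTI alone as primary.

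**Deaths are visible.** In-hospital mortality is a listed outcome and the DSMB sees monthly efficacy and safety data. In the simulation, 62% to 97% of the misleading stay results at 63 and 97 per arm came with significantly higher mortality in the same arm. This limits the harm, but does not correct the stay or OTI comparison. At 63 per arm and 30% vs 20% mortality, 38% of the misleading results come without that warning.

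**The size is assumed.** This is correct. A gap of 10 to 20 points between two masks is large, and equal mortality gives no bias. Pooling both strata (160 per arm) raises the rates to about 20% and 62%, but the plan sizes the strata separately. The near-zero rates for free days follow largely from scoring death as the worst value.

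**Further readings that go too far.**
- *NIV duration as a third biased outcome:* no favourable direction is stated, and NIV is given in sessions. The smaller point is only that endings by recovery, intubation and death are pooled.
- *OTI has no window at all:* the sentence in item 18a can be read as giving OTI the 30 days.
- *Every date needed is already collected:* the article does not say so, and mortality is recorded only in hospital.

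**Conclusion.** The concern holds in a limited form. As written, the plan ranks early deaths as short ICU and hospital stays and counts death without intubation as a non-event for the primary, and nothing in the article corrects either.

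The distortion needs deaths to differ between arms in rate or timing. At the planned stratum sizes and the assumed stays, a 10-point mortality gap raises the rate of false findings for the worse arm from 2.5% to about 10% to 14%, and a 20-point gap to about 28% to 43%. These figures illustrate the mechanism and do not forecast this trial. OTI alone remains a legitimate primary outcome; it needs a companion analysis that shows whether fewer intubations were offset by deaths.

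**What to change.** - **Stay:** analyse ICU-free and hospital-free days to day 30, with in-hospital death by day 30 set to 0, using the Mann-Whitney test already planned. Describe raw stay in survivors alongside. State the day from which the 30 days run.
- **Primary:** keep OTI. State clearly that its window is 30 days, and add OTI or in-hospital death without OTI by day 30 as a sensitivity analysis. It should not replace the primary: with 5% dying without intubation in both arms, its power in the COVID stratum is 74.0%.
- **NIV duration:** report it by how NIV ended (recovery, intubation, death) where that is recorded.

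**Cost:** mostly analysis wording, with no change to the sample size. ICU time, hospital stay, OTI and in-hospital death are already outcomes; how NIV ended is not listed and may need a data field. Free days mix death and stay, hence the description in survivors. Patients discharged alive would be taken as alive to day 30 unless follow-up shows otherwise, and that assumption should be stated.
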